### Intervention outcomes

Socio-demographic, health, and lifestyle data will be collected from the patients through the report of the legal guardians and when possible, the patients themselves. Data of the medical aspects of the study will be collected through the patient's chart, ICU monitors, and direct communication with the multidisciplinary team. The data will be recorded in an appropriate form by properly trained researchers. Researchers who collected study data will not be part of the hospital staff.

All outcomes will be assessed according to the outcome assessment recommendations of Young et al. [25]. The primary outcome will be the length of stay in the ICU. The secondary outcome measures included:

Cross-sectional area and muscle thickness of the rectus femoris and biceps brachii measured by ultrasound, using an 8-MHz 5.6-cm linear transducer array (PLM805, Toshiba Medical Systems, Crawley, UK) immediately after randomization and at intervals of 48 h for 28 days or till discharge from the ICU, whichever occurred earlier. For evaluation of the rectus femoris, the transducer will be placed perpendicular to the long axis of the thigh on its superior aspect, three-fifths of the distance from the anterior superior iliac spine to the superior patellar border [26]. Biceps brachii will be evaluated at the midline between origin and insertion [27]. The transducer will be positioned with slight pressure.Change in muscle strength will be evaluated immediately after randomization, after 3 days and at intervals of 7 days, up to the 28th day or till discharge from the ICU. Muscle strength will be measured using the following: (1) Medical Research Council sum-score (MRC) [28]; (2) handgrip, using a hydraulic dynamometer (Saehan Corporation SH5001, Korea), with the handle pressed for at least 6 seconds in three trials with a 1-min intervals; the highest value of manual grip strength in kilograms (Kgf) will be considered for the analysis [29]; (3) hand-held dynamometer of elbow flexion and knee extension (model 01163; Lafayette Instrument, Ind) [30]; and (4) five Sit to Stand Tests [31].Functional status at 28 days after randomization or discharge from ICU will be measured using the FSS [23], Surgical Optimal Mobilization Score (SOMS) [12], and timed up-and-go score [32].ICUAW will be determined by a score lower than 48 on the MRC sum-score, according to Vanpee et al. [28].Days with mechanical ventilation and mortality at 28 days after randomization or discharge from the ICU.

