## Abstract

The dose of progressive active mobilization is still uncertain. The purpose of this study is to identify if the addition of a protocol of progressive active mobilization with dose and training load control to usual care is effective in reducing the length of stay in intensive care unit (ICU) and the improvement of the functioning, incidence of ICU-acquired weakness (ICUAW), mechanical ventilation duration and mortality rate in patients hospitalized in ICU. It is Double-blind randomised clinical trial. The setting for this trial will be medical and surgical ICU of a university hospital. The study participants will be 118 patients aged> 18 years admitted to ICU for less than 72 hours. Participants will be randomized to either an experimental or control group. The experimental group will undertake addition of a protocol of progressive active mobilization with dose and training load control to usual care, while the control group will undertake only usual care. The primary outcome will be length of ICU stay. The secondary outcomes will be Cross-sectional area and muscle thickness of the rectus femoris and biceps brachii, Change in muscle strength from the baseline, Functional Status, incidence of ICUAW, Days with mechanical ventilation and Mortality. All statistical analyses will be conducted following intention-to-treat principles. It has a detailed description of the dose of exercise, was designed with the strictest methodological criteria. These characteristics allow to investigate with greater certainty the results progressive active mobilization in critical patients, allowing replication and future combinations in meta-analyzes.

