Therefore, the primary endpoint of this RCT will be to identify if the addition of a protocol of progressive active mobilization with dose and training load control to usual care is effective in reducing the length of stay in ICU. The secondary outcomes will be cross-sectional area and muscle thickness of the rectus femoris and biceps brachii, change in muscle strength, functional status, incidence of ICU-acquiredweakness (ICUAW), days with mechanical ventilation, and mortality.

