### Participants

Patients admitted to the ICU of the Universitary Hospital [name] of the Federal University of Bahia (UFBA), Salvador, Bahia, Brazil, who met the eligibility criteria will be recruited in the study. Inclusion criteria: Patients hospitalized in the ICU aged 18 years or more with the following: a minimum functional classification of level 1 (i.e. being able to roll in the bed and bridge); Barthel index [11] recall of at least 70, 2 weeks prior to ICU admission [12]; and the ability to interact with the physiotherapist, determined by at least three positive responses of the following five commands: (1) “Open (close) your eyes,” (2) “Look at me,” (3) “Open your mouth and put out your tongue,” (4) “Nod your head” and (5) “Raise your eyebrows when I have counted to five" [13].

Exclusion criteria included the following: patients with hospitalization time greater than 72 hours before the start of the study; patients with an estimated mortality rate greater than 50% according to Acute Physiology and Chronic Health Disease Classification System II (APACHE II) [12]; patients with increased intracranial pressure or with an history of cardiorespiratory arrest; patients with unstable fractures that hamper the progression of mobilization levels; lower limb amputees; patients with degenerative neuromuscular disease; and those with a history of cerebrovascular accident, traumatic brain injury, or radiotherapy and/or chemotherapy in the last 6 months.

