### Data analysis

For the analysis of demographic and clinical data, descriptive statistics will be used. The data of continuous variables will be analyzed with measures of central tendency and dispersion. The categorical variable data will be analyzed with frequency measurements. To perform the inferential statistics, tests for normality and homogeneity of variance will be performed. Since the data will be normally distributed, analysis of variance (ANOVA) will be used to compare the mean differences of the variables, followed by the Bonferroni post hoc test. If there will be no normal distribution, the Kruskal-Wallis test will be used, followed by the Mann-Whitney post-hoc test. χ2 tests will be used to evaluate the differences in the categorical variables between the groups.

Kaplan-Meier analysis will be used to estimate ICU LOS, mortality, and mechanical ventilation time, and a log-rank will be used to assess the difference between the groups. Poisson or negative binomial model will be used to estimate the incidence rate ratio. Stratified analyses will be performed according to age, initial functional status, and the Acute Physiology and Chronic Health Enquiry (APACHE-II) score to identify potential confounders. Cohen's *d* effect sizes will be also calculated. Before carrying out the analyzes, test methods assumptions will be verified.

Mean and median differences and 95% confidence intervals will calculated. The significance threshold will be used *P* < .05 for each outcome and testing will be used two-sided. The statistical software used will be used IBM SPSS for Windows 21.0. All study analyses will be used performed according to the intention to treat.

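### ICUAW is called an incidence but is defined only as an MRC sum-score below 48, with patients already weak at randomization not separated out, which dilutes the comparison

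*Protocol article*

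**What the plan says.** The Abstract names among the secondary outcomes "incidence of ICUAW, Days with mechanical ventilation and Mortality", and the Introduction repeats "incidence of ICU-acquiredweakness (ICUAW), days with mechanical ventilation, and mortality". Under Intervention outcomes the only definition is "ICUAW will be determined by a score lower than 48 on the MRC sum-score". It has no time point, no condition on the score at entry and no rule for repeated scores.

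The same section sets the MRC schedule: "Change in muscle strength will be evaluated immediately after randomization, after 3 days and at intervals of 7 days", continuing "up to the 28th day or till discharge from the ICU". The MRC sum-score is the first strength instrument listed for those visits, so every patient should have a baseline value.

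Under Participants, the functional entry requirement is "a minimum functional classification of level 1 (i.e. being able to roll in the bed and bridge". Patients may already have spent up to 72 hours in hospital. No MRC threshold applies; the nearest exclusion is degenerative neuromuscular disease. Under Data analysis, chi-square "tests will be used to evaluate the differences in the categorical variables between the groups". A Poisson or negative binomial model for an incidence rate ratio is also mentioned, but it is not tied to any outcome and no person-time is given.

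**The concern.** Incidence means new cases among people who could become cases. A threshold with no baseline condition measures something else: the total of new and pre-existing weakness. Someone who scores below 48 at the randomization visit already meets the definition, whichever arm follows. Such patients add equally to both arms, so they pull the risk ratio toward 1 and cost power. The chi-square test also makes no use of the baseline score that would separate the two groups.

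A second, smaller issue is which score classifies the patient. MRC visits stop at ICU discharge, so the number and timing of scores follow ICU stay, which is the primary outcome. Unless the qualifying visit is fixed, part of an ICUAW difference could reflect stay rather than strength.

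**Working it through.** **The plan's own figure.** The article states no figure for ICUAW. The sample size for stay does reproduce. The common SD is √((4.1² + 4.5²)/2) = 4.305. Then n = 2 × (4.305 × (1.960 + 0.842)/2.5)² = 46.5, so 47 per arm and 94 in all; 94/0.80 = 117.5, so 118. The point below does not affect it.

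**Dilution.** Inputs:
- 47 evaluable patients per arm and two-sided 5% significance, from the article.
- New-case risks of 40% (control) and 20% (intervention): assumed.
- Share b below 48 at entry, 0 to 40%: assumed.
- Patients weak at entry count as events whatever happens later: assumed. This is exact if the baseline score counts, or if they stay weak. Dilution is smaller if some recover before the qualifying visit.

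Formulas: p_C = b + (1 − b) × 0.40; p_I = b + (1 − b) × 0.20; power = Φ((d − 1.96 × SE₀)/SE₁), where d = p_C − p_I, SE₀ uses the pooled proportion and SE₁ the separate ones.

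Example, b = 20%:
- p_C = 0.20 + 0.80 × 0.40 = 0.52; p_I = 0.20 + 0.80 × 0.20 = 0.36; risk ratio 0.36/0.52 = 0.69.
- SE₀ = √(2 × 0.44 × 0.56/47) = 0.1024; SE₁ = √((0.52 × 0.48 + 0.36 × 0.64)/47) = 0.1011.
- Power = Φ((0.16 − 0.2007)/0.1011) = 34%.
- At-risk patients only (47 × 0.80 = 37.6 per arm, 40% v 20%): 47%.

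| Share weak at entry | Control v intervention | Risk ratio | Power, all counted | Power, at-risk only |
|---|---|---|---|---|
| 0% | 40% v 20% | 0.50 | 56% | 56% |
| 10% | 46% v 28% | 0.61 | 44% | 52% |
| 20% | 52% v 36% | 0.69 | 34% | 47% |
| 30% | 58% v 44% | 0.76 | 27% | 42% |
| 40% | 64% v 52% | 0.81 | 22% | 37% |

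Other assumed risks at b = 20%: 30% v 15% gives a risk ratio of 0.73 and power of 22% against 34%; 50% v 25% gives 0.67 and 49% against 61%.

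**Dependence on stay, if any score were to count.** The stay figures, 12.7 ± 4.1 v 15.2 ± 4.5 days, are labelled hospital stay under Sample size calculations. Applying them to ICU stay, with a normal shape, is an assumption. With visits on days 3, 10, 17 and 24, 74% v 88% are still in the ICU on day 10 and 15% v 34% on day 17. Summing over visits gives 1.89 v 2.24 expected post-baseline assessments. Reading the schedule as days 3, 7, 14, 21 and 28 gives 2.31 v 2.67.

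Suppose treatment has no effect on strength and each visit carries a chance q of a new score below 48. The proportion ever below 48 is the mean of 1 − (1 − q)^K over the number of visits K. For q = 5% this is 9.2% v 10.8%, and for q = 20% it is 33.6% v 38.6%, on the first schedule. Across both schedules the gap is 1.6 to 5.0 points, in favour of the shorter-stay arm.

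**Would classifying at ICU discharge remove this?** Not entirely. Take a simulated patient with true MRC 52 ± 5, visit error 2.5 and a decline of 0.15 per day (all assumed), and no treatment effect. Among those at or above 48 at entry, 20.9% v 23.4% are below 48 at discharge, because the score is taken later in the longer-stay arm.

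**The case against.** The strongest objection is that the definition is open rather than wrong. A reader might infer that any score below 48 counts, but the article never says so. Functional status and mortality, described alongside, are tied to 28 days or ICU discharge, and ICUAW may be meant the same way. Which visit classifies a patient is a detail that an article can leave to a fuller document. The word incidence itself suggests new cases, and the baseline score needed to identify them is collected. This stands against any claim that the plan adopts an any-score rule.

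It is also fair that the trial is not powered for ICUAW, that the entry criteria favour patients with some function, and that the share below 48 at entry is unknown. The stay effect is small: a gap of 2 to 5 points compares with a standard error of about 10 points at 47 per arm. Part of such a gap could also be real decline over a longer stay rather than repeated measurement.

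What the objection does not remove is the mismatch between label and definition. Whether the qualifying score is any score or the discharge score, patients below 48 at entry are not separated from new cases, and the stated test ignores their baseline value.

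**Conclusion.** The point holds as a dilution problem in a secondary outcome. Under the stated assumptions, a 10-40% share weak at entry moves a risk ratio of 0.50 to 0.61-0.81. Power falls to 44-22%, where the at-risk patients alone would give 52-37%. The article supplies neither the ICUAW risks nor the share, so only the direction is firm; the size is illustrative, and smaller if patients weak at entry recover before the score that counts.

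A reader might go further and conclude that the ICUAW comparison is biased or cannot be interpreted. The article does not support that. Pre-existing cases fall equally on both arms in expectation, so they weaken the contrast without favouring either arm. The dependence on stay arises only under particular readings of an unspecified visit. It is about 2 to 5 points under assumed inputs if any score counts, and rests on figures labelled hospital stay. It is a reason to fix the visit, and secondary to the dilution.

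**What to change.** Three changes, ideally made before any unblinded data are seen:

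1. Analyse ICUAW in all randomised patients by logistic regression of the post-baseline classification on arm, with baseline MRC as covariate, in place of the unadjusted chi-square test.
2. Report new ICUAW among patients with MRC of at least 48 at the randomization assessment, and show those weak at entry separately by arm. State that this assessment precedes the first study session, so that it is a true baseline.
3. Classify at a scheduled time counted from randomization, using visits already planned: for example the day 3 visit, or the last score on or before a stated day. State how earlier ICU discharge and death are handled. Classification at ICU discharge should be avoided because its timing still follows stay.

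The cost is a change of definition and analysis wording; no new measurement is needed. The new-case analysis drops patients weak at entry, which the adjusted analysis of all patients offsets. An early fixed time captures fewer late cases. A later cut-off captures more, but with fewer patients still in the ICU to be scored, so the day is a trade-off to settle in advance.

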### Sample size calculations

The sample size calculation will be based on a mean difference in the length of hospital stay of 2.5 days; considering a confidence interval of 95%, power of 80%, and a ratio of 1: 1 between the two groups. Based on the averages of the study by Dong et al. [33] (12.7±4.1 vs 15.2±4.5 days), a sample size of 94 patients was obtained, 47 for each group. After adjusting 20% for missing, death, loss to follow-up, and withdrawals, the corrected sample was 118 subjects. The study by Dong et al. [33] was chosen because it had a population similar to that in the present study. Among other aspects of population similarity, the study involved patients able to perform activities independently and with a probability of <50% for death at 6 months. The sample size calculation will be performed using the module that calculates sample sizes to compare two averages available on the website: https://www.openepi.com/SampleSize/SSMean.htm.

This sample also will be sufficient to contemplate the functional independence objective, based on the percentage of patients returning to their functional state at the time of hospital discharge (FSS = 35). A final sample size of 86 patients was obtained, 43 for each group, based on 50% of patients returning to the previous functional state at the time of hospital discharge [34] and assuming that 80% of the patients remained in the intervention group at the time of hospital discharge.

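### Mortality, ventilation days and functional status are timed at day 28 or ICU discharge without saying which; read as the earlier of the two, the window closes at the event the intervention is meant to bring forward

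*Protocol article*

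**What the plan says.** All references are to the protocol article.

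- **Intervention outcomes, last item:** "Days with mechanical ventilation and mortality at 28 days after randomization or discharge from the ICU".
- **Intervention outcomes, function:** "Functional status at 28 days after randomization or discharge from ICU will be measured using the FSS", together with a surgical mobilisation score and the timed up-and-go test.
- **Intervention outcomes, ultrasound:** "at intervals of 48 h for 28 days or till discharge from the ICU, whichever occurred earlier". This is the only outcome for which the choice between the two times is written out. Strength is measured up to day 28 or until ICU discharge, which is similar but less explicit.
- **Intervention outcomes, primary:** "The primary outcome will be the length of stay in the ICU". ICU discharge is therefore the event that ends the primary outcome.
- **Data analysis:** "Kaplan-Meier analysis will be used to estimate ICU LOS, mortality, and mechanical ventilation time", with a log-rank test between groups. How a patient discharged alive from the ICU enters the mortality curve is not stated. χ2 tests are planned for categorical variables in general.
- **Sample size calculations:** the main calculation uses a "mean difference in the length of hospital stay of 2.5 days". The functional objective is sized on recovery at hospital discharge, a third time point that the list of outcomes does not contain.

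Nowhere does the article commit to following patients for vital status or function after they leave the ICU.

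**The concern.** An outcome whose observation period ends at ICU discharge is tied to the primary outcome. If the intervention shortens ICU stay, its patients are watched for less time. Deaths on the ward or at home before day 28 drop out of the count, and more of that period is lost in the arm discharged sooner. Functional status is read earlier after randomisation in that same arm. A reader who wants to know whether a shorter stay was safe, and whether patients were functionally better for it, would be comparing arms over different periods.

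This goes beyond detail that an article may leave to a fuller document. The time point is stated, and it is stated in a form that allows different endpoints.

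**Working it through.** **1. The plan's own figure.** Inputs from Sample size calculations: "12.7±4.1 vs 15.2±4.5 days), a sample size of 94 patients was obtained, 47 for each group" and "considering a confidence interval of 95%, power of 80%, and a ratio of 1: 1 between the two groups"; two-sided 5% from Data analysis.

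- n per group = (1.960 + 0.842)² × (4.1² + 4.5²) / 2.5² = 7.85 × 37.06 / 6.25 = 46.5, rounded up to 47, so 94 in total.
- Inflation for 20% loss: 94 / 0.80 = 117.5, rounded up to 118.

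Both figures reproduce. Nothing in this point alters them.

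**2. Which event closes the window?** Take stay as normal with the planning means and SDs, and the window as the earlier of stay and 28 days.

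- Intervention: (28 − 12.7) / 4.1 = 3.73 SD, so about 0.01% stay beyond day 28.
- Control: (28 − 15.2) / 4.5 = 2.84 SD, so about 0.2% stay beyond day 28.
- A right-skewed (gamma) stay with the same means and SDs gives about 0.2% and 0.8%.

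Discharge ends the window for more than 99% of patients. The mean windows are about 12.7 and 15.2 days, so the intervention arm is observed 2.5 / 15.2 = 16% less.

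**3. Effect on crude mortality with no true effect.** The article gives no mortality figure. Assume a constant hazard h = 0.0107 per day in both arms, chosen so that about 15% of controls die within the window. For a normal stay with mean m and SD s, the counted proportion is 1 − exp(−hm + h²s²/2).

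- Intervention: 1 − exp(−0.1359 + 0.0010) = 12.6%.
- Control: 1 − exp(−0.1626 + 0.0012) = 14.9%.
- Risk ratio: 12.6 / 14.9 = 0.85. With 59 per arm that is about 7.4 against 8.8 deaths.

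Other assumed levels of true 28-day mortality, equal in both arms:

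| True 28-day mortality | Counted, intervention | Counted, control | Risk ratio |
|---|---|---|---|
| 10% | 4.7% | 5.5% | 0.84 |
| 20% | 9.6% | 11.4% | 0.84 |
| 30% | 14.8% | 17.5% | 0.85 |

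The ratio barely depends on the assumed level. With every patient followed to day 28 it is 1.00.

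**4. Effect on the planned log-rank test.** In the same model (equal constant hazard, stay independent of risk, 59 per arm, censoring at the earlier of discharge and day 28), simulated trials give a mean log-rank z of about 0 and 4.4% to 4.8% rejections at the nominal 5%. There is no bias between arms. A crude χ2 comparison of the same deaths shifts only to 6.6% rejections.

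That result depends on discharge carrying no information about risk. If patients with longer stays also carry higher risk, the log-rank drifts slightly against the intervention, because the patients still in the ICU on a given day are a sicker selection in the arm that discharges sooner.

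**5. What the curve estimates.** With censoring at discharge, the Kaplan-Meier value at day 28 extrapolates the in-ICU hazard: 1 − exp(−28 × 0.0107) = 26% (about 24% in simulation), against roughly 15% who died in the ICU. This concerns the absolute level in both arms. It is not a difference between them.

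**6. Function and ventilation.** At the planning means, function is read 2.5 days sooner after randomisation in the intervention arm. The article gives no rate of recovery, so this cannot be turned into a loss of score. For ventilation days the effect is small: ventilation is mostly given in the ICU, and what is missed is mainly re-ventilation after discharge or readmission.

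**The case against.** The strongest reply is that the earlier-of-the-two rule is written only for ultrasound. For mortality, ventilation and function the wording could also mean day 28 for everyone, or two separate readings; on either, a common 28-day horizon exists. This stands in part. The earlier-of-the-two reading is inferred from the neighbouring items and is not certain. But the text does not choose, the readings are different endpoints, and no follow-up after ICU discharge is promised.

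A second reply is that the crude proportions are beside the point, because the test named for mortality is the log-rank. This also stands in part. A reader might infer that a shorter stay automatically lowers measured mortality; step 4 shows that this holds for crude counts and not for the planned test when discharge is non-informative. A reader might also take the 24–26% curve value as bias between arms; it is a question of level common to both.

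A third reply is that function at ICU discharge is a legitimate milestone for an ICU scale. That is right. A reader might infer that earlier assessment must make the intervention look worse, but patients leave when fit to leave, and the article has no data showing a loss of score.

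Finally, the 12.7 and 15.2 days are labelled hospital stay, so the sizes above are illustrative. Under equal hazards, the direction of the crude effect holds for any real reduction in ICU stay.

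**Conclusion.** The point holds as a should-fix on secondary outcomes. The time point for mortality, ventilation days and function is not fixed. On its natural reading, the window closes at ICU discharge for almost every patient and deaths after discharge are not counted.

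- **Mortality:** crude proportions would favour the arm that leaves sooner, by a risk ratio of about 0.85 at the planning figures. This assumes an equal constant hazard that continues after discharge; if the hazard falls after discharge, the distortion is smaller. The log-rank comparison is unbiased only if discharge is non-informative, which is doubtful because discharge is itself a sign of recovery. The curve does not estimate actual 28-day mortality.
- **Function:** compared at different times since randomisation; direction and size of any distortion unknown.
- **Ventilation days:** little affected.

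The documents do not support the stronger conclusion that none of these outcomes could be read as a treatment effect. The primary outcome and the sample size of 94, inflated to 118, are untouched.

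**What to change.** In Intervention outcomes, replace the double time point with one horizon from randomisation:

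- all-cause mortality to day 28 wherever the patient is;
- ventilation days counted from randomisation to day 28.

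In Data analysis, state that patients are not censored at ICU discharge in the mortality analysis.

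Keep functional status at ICU discharge if wanted, but label it a milestone measure and not a fixed-time comparison. Reconcile it with the hospital-discharge time point on which Sample size calculations sizes the functional objective.

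The cost is a change of wording and a record check or telephone call for day-28 status in patients already discharged. No change in sample size is needed. Status after discharge that was never collected may not be recoverable at analysis, so the change is best made before or during recruitment.
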